## Compliance for the 2nd and following attacks

Compliance shall be determined by

- Checking the remaining tablets in returned blisters at D3 by patients. The investigator will count the remaining tablets and in case of discordance the investigator will ask for the reason.
- Dosage of plasma level of desethyl-amodiaquine or lumefantrine. At D3 and D7, a vaccinostyle will be used to collect blood from fingerpick onto filter paper. It will be an exploratory assessment that could be preformed in case of failure or significant intolerance

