**9.2.2. Treatment allocation**

Following the diagnosis of their first episode of uncomplicated malaria, participants will be referred to the study nurse who will be responsible for the treatment group assignment and allocation of the study medications. The study nurse will assign treatment groups as follows:

1. On the randomization list select next study number

2. Scrape the opaque case corresponding to study number in order to discover the allocated treatment

3. Record onto the treatment accountability form the study number, enrollment date, treatment assignment name, and study medication dosages to be given.

4. Store form with the randomization list

5. Fill in the treatment allocation page. After the monitoring of the CRF this form will be attached to the CRF

A patient will be treated by the same treatment for all repeated episodes of uncomplicated falciparum malaria, occurring within a minimal delay of 14 days throughout the study (2 years).

Study investigators involved in patient evaluation and treatment outcome classification will be blinded to treatment assignment.. Only nurses responsible for administration of study drugs will remain unblinded to participant’s assigned treatment regimens.

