## Packaging and labeling

All test drugs (investigational products- IPs) will be stored in their original packaging in the study clinic.Commercial blister packs of 3 tablets for Coarsucam® and 8 tablets for Coartem® will be used. A label with the study reference, patient number (to be filled in) and the statement “product for use in clinical trials” will be affixed to each blister/pack.

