## Treatment accountability and compliance

For the first attack, each dose of the study treatment will be administered by a study nurse, and the patient will be monitored for 30 minutes after administration. If the patient vomits or rejects the treatment within the 30 minutes, the same dose will be re-administered. In the event of repeated vomiting, a replacement treatment will be given as discussed in 9.7.3. Study participants may choose to either be hospitalised (retained at the clinic) for administration of study medications or to commute from home. Participants will be reimbursed for transport to and from the clinic and for meals or other incidental expenses if they are hospitalised for treatment administration. Amounts for reimbursement will be based on the current rates for transport, meals and incidental expenses. Home visitors shall actively follow patients who do not come for scheduled appointments.

For the repeat attacks the 1st intake will be administered at the study clinic and the other intakes will be unsupervised. At day 3, the patient will give the blister to the study nurse who will check the number of remaining tablets in the returned blister. The parent/guardian will inform the clinical team member of any event related to these intakes. In case of vomiting of an unsupervised intake within the 30 minutes, the patient will visit the study clinic where the same dosage will be administered again.

The study nurse shall record the information on the appropriate CRF page. The Monitor in charge of the study then checks the CRF data by comparing them with the Investigational Product which he/she has retrieved and treatment log forms. All steps will be taken to ensure that patients receive treatment in compliance with the protocol.

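### Section 10.3 has the investigator count tablets in returned blisters, against 9.9 and the assessor blinding in 9.2.2; a site that follows it unblinds the assessor for repeat attacks

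*Protocol*

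**What the plan says.** The trial is open, but section 9.2.2 commits to blinded assessment: "Study investigators involved in patient evaluation and treatment outcome classification will be blinded to treatment assignment". It adds: "Only nurses responsible for administration of study drugs will remain unblinded". Section 9.5 keeps the two roles apart by requiring that the dispensing nurse has no part in assessing patients.

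Two sections then describe the D3 tablet check for repeat attacks, where all intakes after the first are unsupervised:

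- Section 9.9: "At day 3, the patient will give the blister to the study nurse who will check the number of remaining tablets in the returned blister". Recording the result in the CRF also falls to the nurse.
- Section 10.3: "The investigator will count the remaining tablets and in case of discordance the investigator will ask for the reason".

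The visit list for D3 of repeat attacks (13.2.3) includes collecting and checking the returned treatment but does not say who does it.

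On packaging, section 9.3 says that test drugs "will be stored in their original packaging in the study clinic" and that "Commercial blister packs of 3 tablets for Coarsucam® and 8 tablets for Coartem® will be used". Section 7.2 has each child receive the same drug at every episode over the two years.

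**The concern.** Sections 9.9 and 10.3 give one task to two different people. Only the 9.9 version fits the blinding rule. Under 10.3, a person who must be blind handles a pack that shows the treatment.

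What is at stake is the repeat-attack comparison, which the study rationale names as a purpose of the trial. Several of its outcomes rest on the investigator's opinion. Effectiveness in later attacks draws on clinical signs graded after an interview by the investigator (10.1.2). Adverse events are graded for severity and judged Yes/No for relationship to the drug by the investigator (11.5). Section 10.2.3 compares these safety indices with each treated episode as the unit of analysis, so repeat attacks enter directly. An assessor who knows the arm can shift such judgments without intending to.

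**Working it through.** The protocol gives no figure to reproduce here. The check is whether the instructions can all be followed, whether the count really reveals the arm, and which outcomes it reaches.

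**1. Can the sections be reconciled as written?**

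| Section | Who handles or counts | Status under 9.2.2 |
| --- | --- | --- |
| 9.5 | Dispensing nurse, not an assessor | May be unblinded |
| 9.9 | Study nurse | May be unblinded |
| 10.3 | Investigator | Must be blinded if assessing |

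They cannot. Appendix 7 defines investigator broadly, so someone who does not assess patients might do the count. But 9.2.2 names only drug-administering nurses as unblinded, so the conflict remains.

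**2. Does the count reveal the arm?** The pack format alone does. The expected count does so too.

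Inputs: doses and tablet strengths from section 9.1, pack sizes from 9.3. Assumption: whole blisters are dispensed, which the protocol does not state.

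- Coarsucam, each weight band from 5 to under 36 kg: the daily dose equals one tablet of the matching strength, so 1 × 3 days = 3 tablets. A fully compliant child returns 3 − 3 = 0.
- Coartem: tablets per course = (daily artemether in mg ÷ 20) × 3 days.
  - Under 15 kg: 40 ÷ 20 × 3 = 6. One blister of 8 leaves 8 − 6 = 2.
  - 15 to under 25 kg: 80 ÷ 20 × 3 = 12. Two blisters leave 16 − 12 = 4.

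Full compliance thus means an empty 3-tablet blister in one arm and an 8-tablet blister format with tablets left over in the other. To recognise discordance at all, the counter must know the expected number, and therefore the drug.

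**3. How long does it last?** The drug does not change between episodes, so an arm learned at D3 of the first repeat attack stays known for the rest of that child's follow-up.

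**4. Which outcomes does it reach?**

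- *Primary endpoint.* It concerns the first attack only. Every first-attack dose is given by a nurse (9.9), and blister return is described only for repeat attacks.
- *Smears.* They are read by technologists outside direct patient care, with a second reader and a third for disagreements (10.1.3).
- *PCR.* Genotyping is laboratory work in Kampala under fixed matching rules (Appendix 6).
- *D3 fever and parasite status in repeat attacks.* These are an electronic thermometer reading and a smear.
- *Graded signs, fever history, adverse event severity and relatedness in repeat attacks.* These depend on interview or judgment and are exposed.

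**The case against.** The strongest reply is that 9.9 is the detailed accountability procedure and already names the nurse, that 9.5 supports it, and that one sentence in 10.3 is a slip. This stands in part. A reader might infer that the protocol as a whole unblinds the assessor at every repeat attack. It does not: that happens only where the site follows 10.3 rather than 9.9. Still, 10.3 is a plain instruction, and staff who obey it break 9.2.2.

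A second reply is that blinding is fragile in any case. The trial is open, parents hold the commercial packs and give most repeat-attack doses at home, once daily in one arm and twice daily in the other, and the investigator interviews parents and checks the patient booklet (10.2.1). This also stands, and it limits what the fix can achieve. It does not justify a protocol instruction that reveals the arm.

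Two further inferences are tempting and not supported:

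- *That the count could influence classification of the first attack when a recurrence at D14 to D28 is treated as a new attack.* Smear, temperature and fever history that define the first-attack failure (Appendix 1) are taken when the recurrence is diagnosed, before the blister comes back at D3 of the new attack. Late clinical and late parasitological failure both count as failures, and PCR is done in the laboratory.
- *That knowing the arm decides whether an adverse event is recorded at all, because 11.2 ties recording of symptoms to drug relationship.* Sections 11.4 and 11.7 say otherwise: new or worsening events count as adverse events, and all are recorded whatever their relationship. The relatedness judgment is exposed under either reading; recording is not shown to be.

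**Conclusion.** The contradiction is real. Section 10.3 cannot be followed by an assessing investigator without breaching 9.2.2, and it conflicts with 9.9 on who does the count. Where a site follows 10.3, the assessor learns the arm at D3 of the child's first repeat attack and keeps that knowledge.

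The reach is modest: secondary, subjective repeat-attack outcomes only. The first-attack non-inferiority analysis is essentially untouched, as are smear and PCR results. No size of bias can be given, because the protocol does not show which section the site would follow or how far judgments would shift. The conclusion rests on two readings of the text: that the investigator in 10.3 is, or may be, the one assessing the child, and that the packs are handed back unmasked, as 9.3 implies. The whole-blister assumption affects only the leftover counts, not the conclusion, since the pack format alone identifies the drug.

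**What to change.** In section 10.3, assign both the tablet count and the question about discordance to the study nurse, in line with 9.9. State there that returned blisters and tablet-count records are kept from the investigator who assesses the child. Section 9.2.2 already has the treatment allocation page attached to the CRF only after monitoring; the count page could be handled in the same way. Section 13.2.3 could name the nurse for collection of returned treatment, so that all three places agree.

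The cost is a wording change and a small step in handling forms. The nurse already does the count under 9.9, so no staff or visits are added. The change removes an avoidable route to unblinding. It does not secure blinding, because parents know the drug and speak to the investigator.

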# Patient safety

## Safety instructions

Safety and tolerability of the treatments will be evaluated by recording Adverse Events (AEs) and grading laboratory and vital signs evaluations. A severity grading scale, based on toxicity grading scales developed by the WHO and the National Institutes of Health, Division of Microbiology and Infectious Diseases, will be used to grade severity of all symptoms, physical exam findings, and haemoglobin results (see Appendix 2 and 3).

All laboratories abnormalities on D28 (ref: Appendix 3)

- Grade 2 or more for biological data
- Clinically significant abnormality (whatever the grade)

have to be followed until resolution or progression has to be stabilized.

For each malaria episode, follow-up for safety will be conducted during the scheduled malaria follow-up visits, and at any unscheduled visit. Follow-up for adverse events reported during a given malaria episode will continue until the patient is re-treated with study medications, or the study ends. If an AE is on going at the time of inclusion for a new malaria episode this AE will be recorded as a concomitant disease at D0 (the AE number recorded at the episode where this AE occurred will be specified to link them). At each episode a new cycle of adverse event assessment and reporting will begin according to the definitions of AE and SAE. Each AE will be considered as one until it has recovered.

## Adverse Events monitoring

All events will be managed and reported in compliance with all applicable regulations, and included in the final clinical study report.

All physical/clinical symptoms described at each visit will be recorded as an adverse event if appears or worsens during the study and is considered to be related to the study drug.

For social reasons a patient may be hospitalized for the first 3 days of the 1st malaria attack (treatment period), this hospitalization will not be reported as an AE/SAE.

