## Safety

### Clinical tolerability:

Incidence and severity of adverse events collected. At each visit, the investigator will ask the patient and parent if he/she has experienced any adverse events since the last visit. Vomiting and diarrhoea will be recorded as adverse event after D3.

For the 2nd and following attacks the patient booklet will be checked by the investigator.

On D0 (except for the 1st attack) blood from a fingerpick will be collected onto filter paper; in case of intolerance to the study drug, levels of desethyl-amodiaquine (DSAQ) or lumefantrine (L) could be assessed to check for the residual quantity of the study drug.

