## Definitions of Adverse Event (AE) and Serious Adverse Event (SAE)

An **Adverse Event** is any untoward medical occurrence in a patient or clinical investigation patient administered a pharmaceutical product and which does not necessarily have to have a causal relationship with this treatment.

A priori, efficacy endpoints as specified in the protocol will not be considered as AEs except if, because of the course or severity or any other features of such events, the Investigator, according to his/her best medical judgment, considers these events as exceptional in this medical condition.

A **Serious Adverse Event** is any untoward medical occurrence that at any dose:

1. • Results in death or;
2. • Is life-threatening or;

Note: The term "life-threatening" in the definition of "serious" refers to an event in which the patient was at risk of death at the time of the event; it does not refer to an event which hypothetically might have caused death if it were more severe.

1. • Requires inpatient hospitalization or prolongation of existing hospitalization or;
2. • Results in persistent or significant disability/incapacity or;
3. • Is a congenital anomaly/birth defect;
4. • Is a medically important event:

Medical and scientific judgment should be exercised in deciding whether expedited reporting is appropriate in other situations, such as important medical events that may not be immediately life-threatening or result in death or hospitalization but may jeopardize the patient or may require intervention to prevent one of the other outcomes listed in the definition above.

Note: Examples of such events are intensive treatment in an emergency room or at home for allergic bronchospasm, blood dyscrasias, convulsions or a asymptomatic increase of ALT (≥10 ULN) that does not result in hospitalization, or development of drug dependency or drug abuse.

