## Identification of adverse events

At each follow-up visit (days 1, 2, 3, 7, 14, 21, 28, and 42, and any unscheduled day), study clinicians will assess patients according to a standardized clinical record form. A severity grading scale, based on toxicity grading scales developed by the WHO and the National Institutes of Health, Division of Microbiology and Infectious Diseases, will be used to grade severity of all symptoms, physical exam findings, and laboratory results as mild, moderate, severe or life threatening (Appendices 2 and 3). Any new event, or an event present at baseline that is increasing in severity, will be considered an adverse event.

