## Obligation of the Investigator regarding safety reporting

***Adverse Events***

All Adverse Events regardless of seriousness or relationship to Investigational Product, spanning from the first visit planned in the Clinical Trial Protocol/signature of the informed consent form, up to the last visit planned in the protocol (D42), are to be recorded on the corresponding page(s) included in the Case Report Form.

Whenever possible, symptoms should be grouped as a single syndrome or diagnosis. The Investigator should specify the date of onset, intensity, action taken with respect to Investigational Product, corrective treatment/therapy given, additional investigations performed, outcome and his/her opinion as to whether there is a reasonable possibility that the Adverse Event was caused by the Investigational Product.

Laboratory, vital signs abnormalities are to be recorded as Adverse Events only if they are medically relevant: symptomatic, requiring corrective treatment, leading to discontinuation and/or fulfilling a seriousness criterion and/or is defined as an AESI.

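### The adverse event recording rules conflict: 11.2 and 10.2.1 keep unrelated symptoms, and all vomiting and diarrhoea up to D3, out of tables that other sections say must contain them

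*Protocol*

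**What the plan says.** Two places in the protocol narrow what becomes an adverse event (AE).

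- Section 11.2: a physical or clinical symptom described at a visit "will be recorded as an adverse event if appears or worsens during the study and is considered to be related to the study drug".
- Section 10.2.1: "Vomiting and diarrhoea will be recorded as adverse event after D3".

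Other places set a wider rule.

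- Section 11.3 defines an AE as an occurrence "which does not necessarily have to have a causal relationship with this treatment".
- Section 11.4, which names the D1, D2 and D3 visits among those at which events are identified: "Any new event, or an event present at baseline that is increasing in severity, will be considered an adverse event".
- Section 11.5 makes relationship a Yes/No judgement on an event already being reported.
- Section 11.7 requires recording of "All Adverse Events regardless of seriousness or relationship to Investigational Product", from consent or first visit to D42.

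Section 14.5.4.1 defines treatment-emergent events from the first dose to D42 of each attack, and lists tables of all and of possibly related events.

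The protocol also disagrees on who counts returned tablets at D3 of a repeat attack. Section 10.3: "The investigator will count the remaining tablets and in case of discordance the investigator will ask for the reason". Section 9.9: "the patient will give the blister to the study nurse who will check the number of remaining tablets". Section 9.2.2: "Study investigators involved in patient evaluation and treatment outcome classification will be blinded to treatment assignment".

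**The concern.** Clinical tolerability is a secondary objective for the first attack and for repeated attacks (section 6.2). Section 10.2.1 measures it by the incidence and severity of collected AEs, and section 10.2.3 compares it between arms episode by episode. The rule for what gets onto the AE form therefore decides what is compared.

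A relatedness condition applied before recording turns a judgement that should describe an event into one that decides whether the event exists in the AE data. A cut-off after D3 leaves out vomiting and diarrhoea during the days on which the drugs are taken. Because the same document also tells staff to record everything, different assessors may apply different rules, and the resulting tables would be hard to interpret.

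The tablet count is a lesser, related matter. If the person who judges relatedness also handles the returned pack, that judgement may no longer be blind.

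**Working it through.** No figure in the plan is at issue and no arithmetic applies. The check sets the rules side by side.

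**1. What each set of rules does with the same event**

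| New or worsened event | Under 11.2 and 10.2.1 | Under 11.3, 11.4, 11.5 and 11.7 |
|---|---|---|
| Symptom judged unrelated, any day | not an AE | AE, relationship No |
| Symptom other than vomiting or diarrhoea, D0–D3, judged related | AE | AE |
| Vomiting or diarrhoea, D0–D3, however judged | not an AE | AE |
| Vomiting or diarrhoea after D3, judged related | AE | AE |

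The first and third rows conflict. No section gives an order of precedence. Section 11.7 does state an exception for laboratory and vital-sign abnormalities, but none for symptoms.

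**2. The D3 cut-off against the dosing days.** Both treatments last three days (section 9.1), and the flow chart in section 2.1 places study treatment on D0, D1 and D2. A rule that starts after D3 therefore leaves out the whole dosing period for these two symptoms, although the window in 14.5.4.1 is already open.

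**3. Effect on the planned tables.** If 11.2 is applied, every visit symptom that reaches the form has already been judged related. For symptoms, the tables of all events and of possibly related events then nearly coincide, and the Yes/No field of 11.5 carries little information. If 10.2.1 is applied, D0–D3 vomiting and diarrhoea can enter no treatment-emergent table.

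**4. What is still collected.** Vomiting and diarrhoea are on the list of symptoms graded systematically (section 10.1.3). Repeated vomiting or rejection is recorded as a reason for discontinuation (section 9.7.3), and these children stay in the safety population (section 14.4.2). The table list in 14.5.4.1 uses neither the grades nor those reasons. Children with double vomiting or rejection at the first intake are also outside the ITT population (section 14.4.1), so under 10.2.1 this early intolerance is absent from the efficacy analysis and the AE tables alike. In repeat attacks there are no scheduled D1 and D2 visits (section 2.1), so the first scheduled grading after dosing starts is at D3.

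**5. Size.** The protocol gives no rate of vomiting, diarrhoea or unrelated symptoms in either arm. The number of events lost, and any effect on the between-arm difference, cannot be computed.

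**6. The tablet count.** Section 10.3 gives it to the investigator and section 9.9 to the nurse. Blister packs hold 3 tablets for one drug and 8 for the other (section 9.3), so whoever handles the pack can tell the drug. A child keeps the same drug for later attacks (section 7.2), so that knowledge carries forward.

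**The case against.** The best defence is that these rules are a loosely worded attempt to keep the symptoms of acute malaria out of the AE data. Section 11.3 says that efficacy endpoints are in principle not AEs unless exceptional for the condition, and the synopsis lists the evolution of graded baseline symptoms as a measure of clinical efficacy. That is a plausible motive, and it weakens 11.3 as support for the wider rule. It does not resolve the conflict: the carve-out mentions neither relatedness nor D3, and 11.4 already deals with symptoms present at baseline by requiring that they worsen.

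It is also fair that the trial is declared open, that serious events, AEs of special interest and laboratory abnormalities have their own rules, and that the primary endpoint is not involved.

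Three stronger readings are tempting but not supported.

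- A reader might infer that all intolerance on dosing days disappears. Only vomiting and diarrhoea are removed outright; nausea, pruritus, weakness and other symptoms on D0–D3 still become AEs if judged related.
- A reader might infer that the data are lost and an arm difference in early vomiting would show as none. Grades and discontinuation reasons remain in the case report form and could be tabulated. What the protocol lacks is a table that uses them, and in repeat attacks the D1–D2 grades.
- A reader might infer that the causality assessor is in fact unblinded. Appendix 7 defines an investigator as any medical person involved in the conduct of the study, so the person counting tablets under 10.3 need not be the one judging relatedness. The documents show a conflict of roles, confined to repeat attacks, and not more.

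**Conclusion.** The contradiction stands. Sections 11.2 and 10.2.1 cannot be followed together with 11.4, 11.5 and 11.7, nor do they fit the treatment-emergent window and paired tables of 14.5.4.1. If the two narrow rules are the ones applied, which is the assumption behind the consequence, visit symptoms judged unrelated and all D0–D3 vomiting and diarrhoea are missing from the planned comparison of AEs, a stated secondary objective. If sites apply the wider rules, nothing is lost; if practice is mixed, AE counts depend on which rule an assessor followed.

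The effect is confined to symptom counts in the AE tables and cannot be sized from the document. It should be fixed, but it does not threaten the primary non-inferiority analysis. The tablet-count conflict between 10.3 and sections 9.2.2 and 9.9 is real and secondary.

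**What to change.** - **Section 11.2:** delete the condition that a symptom must be considered drug-related. Keep relatedness as the separate field that 11.5 already provides.
- **Section 10.2.1:** record vomiting and diarrhoea as AEs from the first dose whenever they are new or worse than the D0 grade.
- **Minimum alternative:** if the sponsor wants to keep the narrower rules, state them as an explicit exception in 11.7 with the reason, and add to 14.5.4.1 a by-arm table of graded vomiting and diarrhoea on D0–D3. This is also consistent, but the table would be weaker for repeat attacks, which have no scheduled D1 and D2 grading.
- **Section 10.3:** assign the tablet count to the study nurse, in line with 9.9 and with the blinding of evaluators in 9.2.2.

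The cost is a change of wording in the protocol and the case report form instructions, and more AE lines to enter. Some of the added lines will be malaria symptoms that first appear or worsen after D0; the relationship field and the comparison between randomised arms are there to handle them. No new visit is needed, since symptoms are already graded at D0 and at each later visit.
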